**Table 2. Study drug product and placebo**

| Study Drug                          | ShK-186                                                                                                      | Placebo                                       |
|-------------------------------------|--------------------------------------------------------------------------------------------------------------|-----------------------------------------------|
| Form                         | Solution for subcutaneous injection following dilution in normal saline; packaged in a single-use glass vial | Preservative-free normal saline for injection |
| Strength                     | 1 mg/mL                                                                                                      | 0.9%                                          |
| Manufacturer of Drug Product | [REDACTED]                                                                                                   |                                               |

The lot numbers for the study drugs will be provided to the clinical site by the supplier/manufacturer/distributor/CRO.

### 8.2 Study Drug Packaging, Labeling, Storage, Shipping, and Preparation

The study drug will be shipped to the site from Sherpa Clinical Packaging or the CRO in vials containing 0.65 mg of ShK-186 at a concentration of 1 mg/mL. The vials will be stored frozen at  $\leq -20 \pm 5^{\circ}\text{C}$  under secure conditions and protected from light. Details of study drug/placebo packaging, labeling, storage, shipping, and preparation will be provided in a separate Pharmacy Manual.

### 8.3 Study Drug Administration

Following randomization, subjects will receive twice-weekly 0.3 mL SC doses of placebo (normal saline for injection) or ShK-186 as follows (9 total doses):

**Group 1:** Placebo SC injection twice weekly for 4 weeks (9 doses)

**Group 2:** 30 µg SC injection of ShK-186 twice-weekly for 4 weeks (9 doses, 270 µg total exposure);

**Group 3:** 60 µg SC injection of ShK-186 twice-weekly for 4 weeks (9 doses, 540 µg total exposure);

Appropriate unit doses, as described above, will be administered to the subcutaneous abdominal fat pad of each subject excluding the areas immediately surrounding the navel or waistline. Successive injections will be administered to different sites by rotating between the left/right and upper/lower quadrants of the abdomen. For each dose, the subject's actual time will be recorded in the source documents and transcribed into the CRFs. Further details are provided in the study manual.

#### **8.4 Study Drug Accountability**

An unblinded staff member will maintain an accurate record of the receipt of the test materials as shipped by the Sponsor (or designee), including the date received. One copy of this receipt will be returned to the Sponsor (or designee) when the contents of the test material shipment have been verified. In addition, an accurate drug disposition record will be kept, specifying the amount dispensed to each subject and the date of dispensation.

This drug accountability record will be available for inspection at any time by the unblinded monitor. At the completion of the study, the original drug accountability record will be available for review by the Sponsor upon request. Drug inventory and accountability records will be maintained at each site as per GCP/ICH guidelines.

#### **8.5 Study Drug Handling and Disposal**

At the completion of the study, all unused drug supplies will be returned to the Sponsor (or designee) or disposed of by the study site, per the Sponsor's (or designee's) written instructions.

## **9 STATISTICAL ANALYSES OF SAFETY DATA AND DISEASE ACTIVITY DATA**

### **9.1 Safety Data**

Safety measures will include vital signs, physical examinations, adverse events, serum chemistry, hematology, urinalysis and evaluation of antibodies to ShK-186. Descriptive statistics will be used in the evaluation of safety parameters. Data on antibodies to ShK-186 will be analyzed as described in Section 12.2. Otherwise, no formal statistical analyses are planned.

### **9.2 Pharmacokinetic Data**

For each group, summary statistics including n, min, max, arithmetic mean and/or median, and standard deviation will be presented for concentration/time,  $C_{\max}$  and  $T_{\max}$ . No inferential statistics will be done in this study.

### **9.3 Disease Activity Data**

Disease activity parameters will be measured at various timepoints. Disease activity variables include Investigator and patient global assessment of psoriasis, patient quality of life assessment (using DLQI), patient assessment of disability (using PDI), measurement of psoriasis using PASI component measurements (erythema, induration and desquamation of psoriatic lesions), percent BSA involved and target lesion assessments. Additionally, serum and PBMC biomarkers and lesional biopsy assessments will be performed serially and compared to pre-treatment and non-lesional samples.

Descriptive statistics will be used in the evaluation of disease activity measures. Improvement from baseline in disease activity measures will be evaluated for each timepoint where disease activity parameters are measured.

### **9.4 Sample Size**

The sample size chosen for this study was based upon precedent set by other studies of a similar nature and was not based on power calculations.

## **10 DISEASE ACTIVITY ASSESSMENT**

### **10.1 Dermatology Quality of Life (DLQI) Questionnaire**

The DLQI is a simple 10-question validated questionnaire which will be completed on Day 1 and during study visits on Day 15, Day 32, and Day 57. The questionnaire is provided in Appendix B.

### **10.2 Psoriasis Area Severity Index (PASI)**

Psoriasis Area Severity Index is a scale from 0 to 72 that is regularly used in plaque psoriasis studies. Refer to Appendix C for a complete description of this scale. PASI will be evaluated on Day 1 and during study visits on Day 15, Day 32, and Day 57.

### **10.3 Body Surface Area (BSA)**

The BSA affected with psoriasis will be evaluated by a dermatologist. As a reference, the area of the whole palm is counted as 1% BSA.

### **10.4 Psoriasis Disability Index (PDI)**

The PDI is a simple 15-question validated questionnaire which will be completed on Day 1 and during study visits on Day 15, Day 32, and Day 57. The questionnaire is provided in Appendix D.

### **10.5 Investigator Global Assessment of Psoriasis**

The IGA is a 5-point scale to be used by the Investigator to evaluate psoriasis which will be completed on Day 1 and during study visits on Day 15, Day 32, and Day 57. The scale ranges from 0 (“clear”) to 4 (“severe”). The assessment scale is provided in Appendix E.

### **10.6 Patient Global Assessment of Psoriasis**

The patient global assessment is a 10 point scale to evaluate psoriasis severity from 0 (“none”) to 10 (“severe”) which will be completed on Day 1 and during study visits on Day 15, Day 32, and Day 57. The scale is provided in Appendix F.

### **10.7 Target Lesion Investigator Global Assessment**

The target lesion assessment will evaluate a target lesion for erythema, induration and scaling, on a scale of 0 (best) to 4 (worst), using the Target Lesion Investigator Global Assessment scale presented in Appendix G. Target lesion assessments will be completed on Day 1 and during study visits on Day 15, Day 32 and Day 57.

## **11 ASSESSMENT OF PHARMACOKINETICS**

### **11.1 Pharmacokinetic Analysis**

For each subject, the following PK parameters will be calculated after first and final dose administrations (maximum recorded concentration and the time of the maximum recorded concentration), whenever possible, based on the plasma concentration versus time of ShK-186 and its metabolite ShK-198:

$C_{\max}$  Maximum observed plasma concentration.

$T_{\max}$  Time to maximum plasma concentration.

For samples collected prior to dose administration on Day 15 and 57, the trough plasma drug concentration will be reported.

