| 
Assessments:
 
Safety and Immunogenicity:
 
Vital signs, physical examinations, adverse events (AEs), serum chemistry, hematology, urinalysis, and antibodies to ShK-186.
 
Pharmacokinetics (abbreviated analysis to be performed by a secondary laboratory/Kineta):
 

• Maximum observed plasma concentration (<math>C_{max}</math>)

• Time to maximum plasma concentration (<math>T_{max}</math>)

• Trough plasma concentrations pre-dose on Day 15 and Day 57

 
Disease Activity:
 

• Change from baseline for Investigator and patient global assessments of psoriasis, DLQI and PDI

• Change from baseline for PASI score components (erythema, induration, and desquamation of skin of head, trunk and extremities)

• Change from baseline for % BSA involved

• Change from baseline in target lesion severity scores for target psoriatic lesion

 
Biomarker Analysis (to be performed by a secondary laboratory/Kineta):
 

• Change from baseline for psoriatic plaque histology

• Change from baseline for immune cell populations in psoriatic plaque by immunohistochemistry

• Change from baseline in cytokine expression in psoriatic plaque by qPCR

• Change from baseline for plasma cytokines and chemokines by Multiplex Immuno Assay (Luminex)

 |

- Change from baseline for IL-17A, F and A/F and other cytokines in serum by Single Molecule Counting technology (Singulex)
- Change from baseline in gene expression in whole blood samples (Tempus™)
- Change from baseline in peripheral T cell sub-populations by FACS

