### **3.4 Rationale for Dose Selection**

In the previous studies (single dose 186-01 and 4-week multiple dose 186-02), the safety and tolerability of ShK-186 was evaluated at doses of 5, 15, 30 and 60 µg.

In these studies, ShK-186 was generally well tolerated at all dose levels. In the 186-01 study, group-median exposures following administration of the 15, 30 and 60 µg dose were 478, 848 and 1420 pg\*h/mL, respectively, encompassing the target therapeutic range based on animal efficacy models.

This study is further exploring the 30 and 60 µg doses in subjects with active plaque psoriasis.

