#### 5.1.2 Estimated Study Duration

Each subject will be screened within 30 days of the Baseline visit (Day 1, Dose 1). Each subject will receive placebo or ShK-186 twice weekly for 4 weeks followed by a 4 week follow-up period.

A study schematic is presented in [Figure 1](#). A study flow chart is presented in [Appendix A](#).

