**Figure 1. Study schematic for each cohort.**

|             | Screening* | Biopsy Collection | Dose Administration             | Evaluations                                | Evaluation and End of Study Procedures |
|-------------|------------|-------------------|---------------------------------|--------------------------------------------|----------------------------------------|
| Days | -30 to -1  | -7 to -1          | 1, 4, 8, 11, 15, 18, 22, 25, 29 | 1, 2, 4, 8, 11, 15, 18, 22, 25, 29, 32, 43 | 57                                     |

\*Screening will occur within 30 days of the first dose (Baseline, Day 1) and prior to biopsy collection and randomization. There is no Day 0 in the schedule.

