**14.1.7 Evaluations and procedures on Day 29**

The following procedures will be performed on Day 29.

Prior to Study Drug Administration (Predose Procedures):

1. interim medication/medical history;
2. symptom directed physical examination;
3. vital signs (including temperature, respiratory rate, and supine blood pressure and pulse);
4. AE evaluations;
5. plasma sample for study drug concentration;
6. clinical laboratory evaluations (including Chem-20, CBC, and UA);
7. serum sample for assessment of antibodies to ShK-186;
8. whole blood collection for biomarkers: PBMCs, plasma, serum and whole blood sample for RNA (TEMPUS™).

Study Drug Administration (Time Recorded)

Post-Dose Procedures:

At 5 minutes post dose ( $\pm 1$  min):

9. plasma sample for study drug concentration.

At 15 minutes postdose ( $\pm 5$  min):

10. plasma sample for study drug concentration.

At 30 minutes postdose ( $\pm 5$  min):

11. plasma sample for study drug concentration.

At 1 hour postdose ( $\pm 10$  min):

12. plasma sample for study drug concentration.

At 2 hours postdose ( $\pm 15$  min):

13. vital signs (including temperature, respiratory rate, and supine blood pressure and pulse);
14. AE evaluations;
15. plasma sample for study drug concentration
16. whole blood collection for biomarkers: PBMCs, plasma, serum and whole blood sample for RNA (TEMPUSTM).

At 4 hours postdose ( $\pm 15$  min):

17. plasma sample for study drug concentration.

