#### **14.1.9 End of Study Evaluations and Procedures (Day 57)**

The following procedures will be performed at the End of Study visit:

1. interim medication/medical history;
2. routine physical examination (including neurologic exam);
3. vital signs (including temperature, respiratory rate, and supine blood pressure and pulse);
4. AE evaluations;
5. patient and Investigator global assessments of psoriasis;

6. patient quality of life assessment (DLQI);
7. patient assessment of disability (PDI);
8. %BSA, Psoriasis Area and Severity Index (PASI) and target lesion assessments;
9. plasma sample for study drug concentration;
10. clinical laboratory evaluations (including Chem-20, CBC, and UA);
11. whole blood collection for biomarkers: PBMCs, plasma, serum and whole blood sample for RNA (TEMPUS™);
12. photographic documentation of target lesion that has been assessed throughout, biopsied lesion(s), as well as psoriasis-involved body areas (Subjects will be instructed to abstain from the use of emollients for 24 hours prior to the scheduled photography);
13. serum sample for assessment of antibodies to ShK-186;
14. serum pregnancy test (female subjects only);

Subjects that prematurely discontinue from study should complete all assessments for the scheduled visit and all End of Study assessments.

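### The PK section and the synopsis define a pre-dose trough on Day 57, when no dose is given, and leave the Day 29 pre-dose sample off the trough list

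*Protocol*

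**What the plan says.** Two places in the protocol define the trough, and they agree with each other. Section 11.1 (Pharmacokinetic Analysis) reads: "For samples collected prior to dose administration on Day 15 and 57, the trough plasma drug concentration will be reported". The synopsis, in the pharmacokinetics list under Assessments, reads: "Trough plasma concentrations pre-dose on Day 15 and Day 57".

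The schedule says something different about Day 57. Figure 1 gives the dose administration days as "1, 4, 8, 11, 15, 18, 22, 25, 29", and the dose row of the Appendix A flow chart marks the same days. Section 5.1.2 describes the course as follows: "Each subject will receive placebo or ShK-186 twice weekly for 4 weeks followed by a 4 week follow-up period". Section 14.1.9 covers Day 57 and opens: "The following procedures will be performed at the End of Study visit". Its list includes a plasma drug sample but no study drug administration.

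On Day 29, Section 14.1.7 lists "plasma sample for study drug concentration" as item 5 of the procedures before dosing, and Appendix A marks a plasma PK sample that day. Neither trough statement mentions it.

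**The concern.** A trough is the concentration just before the next dose of a repeated regimen. No dose follows on Day 57, so a sample before dosing on that day does not exist. What is drawn is a concentration at the end of a four-week off-drug period.

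The sample that does fit the definition late in treatment, before the Day 29 dose, has no trough label. The only true trough on the list is therefore the mid-treatment one on Day 15.

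Drug exposure after repeated dosing is the first secondary objective in Section 4.2. If the text is followed literally, a table headed as troughs would show an on-treatment value on Day 15 and a post-treatment value on Day 57. A reader who did not go back to the schedule could take a lower Day 57 figure as trough exposure declining under continued dosing. Antibody samples are taken on those same two days, among others (Section 12.1), so such a decline could also be wrongly linked to antibody formation.

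**Working it through.** No formula is needed beyond schedule arithmetic.

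**Inputs**
- Dosing days: 1, 4, 8, 11, 15, 18, 22, 25, 29 (Figure 1; Appendix A, dose row).
- Plasma PK samples not tied to a post-dose time: Days 1, 15, 29 and 57 (Appendix A; Sections 14.1.3, 14.1.6, 14.1.7 and 14.1.9).
- Window for visits after Day 29: plus or minus 1 day (Section 14.1; Appendix A).
- Planned subjects: 24, randomized 5:5:2 (Section 5.1).

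**Step 1: check the dosing days against the plan's own totals.** The list has 9 days. 9 × 30 µg = 270 µg and 9 × 60 µg = 540 µg. Section 8.3 gives 9 doses and these same totals, so the list is complete and there is no tenth dose on Day 57.

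**Step 2: time since the previous dose.** This is the sample day minus the most recent earlier dosing day.

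| Sample | Previous dose | Interval | Named as trough? | Dose follows that day? |
|---|---|---|---|---|
| Day 15 pre-dose | Day 11 | 15 − 11 = 4 days | Yes | Yes |
| Day 29 pre-dose | Day 25 | 29 − 25 = 4 days | No | Yes |
| Day 57 | Day 29 | 57 − 29 = 28 days | Yes | No |

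With the window, Day 57 runs from 56 − 29 = 27 to 58 − 29 = 29 days after the last dose.

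**Step 3: compare.** Days 15 and 29 have the same scheduled interval, so they form a like-for-like pair. Day 57 comes at 28 / 4 = 7 times that interval.

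**Step 4: who is affected.** 24 × 10/12 = 20 subjects are planned on active drug, so the mislabelled value would be reported for up to 20 subjects.

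**The case against.** The strongest reply is that this is a labelling slip with little behind it, and much of that stands.

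- **The data are not lost.** A reader might infer that the end-of-dosing trough disappears from the report. The documents do not support this. The Day 29 pre-dose sample is collected, and Sections 9.2 and 11.2 plan per-group summaries of concentration over time, where its value can appear. What is missing is its designation as a trough.
- **Repeated-dose exposure can still be examined.** It is tempting to say that the trial cannot address exposure after repeated doses or look for accumulation. Section 11.1 derives Cmax and Tmax after both the first and the final dose, and the post-dose sampling times on Days 1 and 29 are identical (5, 15 and 30 minutes; 1, 2 and 4 hours). That comparison does not depend on the trough sentence.
- **The absence of an AUC is not an error.** Section 3.4 expresses earlier exposure in pg*h/mL, so one might expect an AUC here. But the synopsis calls this an abbreviated PK analysis, the objective does not promise an AUC, and the Section 3.4 figures come from an earlier single-dose study. They have no bearing on the Day 57 label.
- **The Day 57 level is unknown.** The protocol gives no half-life or assay limit. One may say that the sample is post-treatment, but not that the drug will be undetectable. Nor do the documents show that a 4-day trough will be measurable.

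The flow chart may explain the slip. Appendix A places the Day 57 plasma sample in its block of pre-dose procedures, but that block also holds informed consent and the Day 32 and Day 43 assessments. It is a layout heading and does not make Day 57 a dosing day.

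None of this removes the contradiction. The same impossible day stands in both places that define the parameter. An analysis plan that followed the protocol would carry it forward.

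**Conclusion.** The point holds as a contradiction between the trough definition and the protocol's own schedule. Section 11.1 and the synopsis call Day 57 pre-dose. Figure 1, Section 14.1.9 and Appendix A show that it is not. The value reported there would be a follow-up concentration about four weeks after the last dose, set beside a 4-day trough, while the matching 4-day sample on Day 29 goes unnamed.

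Severity is minor to moderate. Trough concentration is a descriptive secondary measure. Section 9.2 plans no inferential PK statistics, and the sample size rests on precedent (Section 9.4). The harm is a possible misreading of the trough table, not a loss of data.

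The conclusion rests on dosing and sampling taking place on the scheduled days. Section 14.1 allows missed or moved doses with the sponsor's approval, which could change the interval for an individual subject but would not turn the scheduled Day 57 visit into a dosing visit.

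**What to change.** Reconcile the two trough statements with the sampling schedule:

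1. In Section 11.1 and in the pharmacokinetics list of the synopsis, define the reported troughs as the pre-dose concentrations on Day 15 and Day 29.
2. In the same two places, describe the Day 57 sample as a follow-up concentration 28 days after the last dose (27 to 29 days with the visit window), and report it separately from the troughs.

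The cost is wording in two places and the matching table labels. Every sample needed is already scheduled, and dosing does not change.

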### **11.2 Statistical Analysis of Pharmacokinetic Data—Descriptive**

For each group, summary statistics including n, min, max, arithmetic mean and/or median, and standard deviation will be presented for concentration/time,  $C_{\max}$  and  $T_{\max}$ . No inferential statistics will be done in this study.

## **12 ASSESSMENTS OF IMMUNOGENICITY**

### **12.1 Immunoassay – Anti-Drug Antibody**

Serum samples will be collected from each study subject pre-dose on Day 1, on Day 15, Day 29 and End of Study. Serum will be evaluated for binding ADA using an ELISA-based method. Each positive serum sample will be evaluated for ADA specificity by repeating the ELISA in the presence of an excess of ShK-186. Confirmed positive, specific serum samples will be titered by serial dilution, and a numerical titer will be assigned.

### **12.2 Statistical Analysis of Immunoassay Data—Descriptive**

The relationship between dose and antibody titer will be evaluated using the Mann-Whitney test. The relationship between antibody titer and drug  $C_{\max}$  will be evaluated using Spearman's Rank Order correlation. Any statistical results resulting from exploratory analysis will be interpreted in view of their exploratory nature.

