**Statistical methods:**

Descriptive statistics will be calculated on the safety and efficacy parameters; no formal statistical analyses are planned.

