## 5 INVESTIGATIONAL PLAN

### 5.1 Overall Study Design and Plan: Description

This is a double blind, placebo controlled study evaluating two dose levels (30 and 60 µg) of ShK-186. A total of 24 subjects with active plaque psoriasis are to be randomized 5:5:2 to receive either ShK-186 60 µg, 30 µg or placebo twice weekly by subcutaneous injection (9 doses total).

Potential subjects will be screened to assess their eligibility to enter the study within 30 days prior to the Baseline visit (first dose).

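### The planned Spearman correlation of antibody titre with Cmax takes no account of dose, so a dose effect on both can mimic or hide an antibody effect on exposure

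*Protocol*

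**What the plan says.** Section 12.2 fixes two analyses of the antibody data. For dose: "The relationship between dose and antibody titer will be evaluated using the Mann-Whitney test". For exposure, the relation between titre and drug Cmax "will be evaluated using Spearman's Rank Order correlation". It adds: "Any statistical results resulting from exploratory analysis will be interpreted in view of their exploratory nature".

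Other sections supply the context:

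- **Design (5.1).** Two active doses, 30 and 60 µg, are set against placebo under blinding. On numbers the section says "A total of 24 subjects with active plaque psoriasis are to be randomized 5:5:2", which gives 10, 10 and 4.
- **Exposure and dose (3.3, 3.4).** Single-dose exposure was broadly proportional to dose. Median exposures in the first-in-human study were 848 pg·h/mL at 30 µg and 1420 pg·h/mL at 60 µg.
- **Cmax (11.1).** Calculated after the first and the last dose, Days 1 and 29.
- **Antibodies (12.1).** Sampled on Days 1, 15, 29 and at end of study. Only confirmed positive samples receive a titre.
- **Scope of testing.** Section 9.1 refers the antibody data to 12.2 and rules out other formal analyses. The synopsis has no such exception ("no formal statistical analyses are planned"), and Section 9.2 says "No inferential statistics will be done in this study", as does 11.2.

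Section 12.2 does not say whether the correlation is taken within or across doses, which Cmax day goes with which antibody day, where antibody-negative samples rank, or which two groups the Mann-Whitney test compares.

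**The concern.** The useful question is whether antibodies reduce exposure. Dose is a cause of Cmax. Titre may also depend on dose, and the first sentence of 12.2 sets out to test that. If both hold, dose confounds the pooled correlation. Subjects on 60 µg then tend to have both the higher Cmax and the higher titre, which pushes the coefficient upwards. A true loss of exposure pushes it downwards. The two can cancel, or the dose effect can win.

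Immunogenicity is part of the primary objective (4.1), and these are the only tests the protocol names. A null or positive coefficient could be read as evidence that antibodies leave exposure intact when the data cannot show that. Because 12.2 names the method, this is a poorly fixed choice and not merely a detail left open.

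**Working it through.** **No planned figure to reproduce.** Section 9.4 bases the sample size on precedent. The allocation is consistent: 24 × 5/12 = 10, 24 × 5/12 = 10, 24 × 2/12 = 4.

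**Inputs from the protocol.** 10 + 10 active subjects; Cmax on Days 1 and 29; exposure ratio 1420/848 = 1.67. That ratio is for total exposure, so using it for Cmax is an assumption; 2.0 is exact dose proportionality.

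**Inputs assumed.** Antibody-positive rates of 20% at 30 µg against 60% at 60 µg, and 40% against 80%; titre one doubling higher at 60 µg; between-subject log SD 0.35; within-subject log SD 0.2 to 0.4; antibodies change Day 29 log Cmax by 0 or −0.5. The latter is a loss of 1 − exp(−0.5) = 39%.

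**Step 1: size of the confounding.** With equal arms, the share of 60 µg subjects is:

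- rates 20/60: 0.6/0.8 = 0.75 among positives, 0.4/1.2 = 0.33 among negatives, difference 0.42;
- rates 40/80: 0.8/1.2 = 0.67 among positives, 0.2/0.8 = 0.25 among negatives, difference 0.42.

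The dose effect on log Cmax is ln 1.67 = 0.51 to ln 2.0 = 0.69. Dose alone therefore makes positives differ from negatives by 0.42 × 0.51 = +0.21 to 0.42 × 0.69 = +0.29 on the log scale. With a true effect of −0.5, the pooled contrast shrinks to between −0.29 and −0.21. A 39% loss then looks like one of about 19–25%.

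**Step 2: why the within-subject ratio avoids this.** For subject *i*:

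- log C(Day 1) = mean + dose term + subject term + error;
- log C(Day 29) = mean + dose term + subject term + antibody effect + error.

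The difference leaves the antibody effect plus two errors. Its noise SD is √2 × 0.2 = 0.28 or √2 × 0.4 = 0.57, so a 0.5 effect is 1.8 or 0.9 noise SDs. The gain depends strongly on the within-subject SD.

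**Step 3: simulated rejection rates, active subjects, nominal 5%.**

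| Method | No antibody effect | 39% loss of Day 29 Cmax |
|---|---|---|
| Pooled Spearman, titre and Cmax | about 14–28% | about 4–19% |
| Spearman, titre and Day 29/Day 1 ratio | about 5% | about 30–91% |

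The range for the ratio reflects within-subject SDs of 0.2 to 0.4. A gap between the two antibody rates wider or narrower than 40 points raises or lowers the pooled false-positive rate.

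**Step 4: a second model as a check.** Here titre is continuous without ties, the between-subject CV of Cmax is 30–50%, and the Cmax ratio is again 1.67–2.0. Titre shifts between doses by 0, 1 or 2 SD.

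| True within-dose correlation | Titre shift | Pooled rho | Pooled rejection | Ranked within dose |
|---|---|---|---|---|
| 0 | 0 | about 0 | about 5% | rho 0.00, 4–6% |
| 0 | 1 SD | 0.22 to 0.36 | 15–35% | same |
| 0 | 2 SD | 0.35 to 0.58 | 34–84% | same |
| −0.5 | 0 | −0.40 to −0.28 | 24–44% | rho about −0.44, 47–53% |
| −0.5 | 1 SD | −0.12 to +0.11 | 4–8% | same |
| −0.5 | 2 SD | +0.08 to +0.38 | 5–37% | same |

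The first row shows no bias when titre is unrelated to dose. The last two show a real negative association vanishing or changing sign. Ranking within dose removes the problem in every row.

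**The case against.** **What stands.** The analyses are labelled exploratory, no decision rule uses them, and an SAP not shown may stratify. The bias needs titre to depend on dose, and the protocol gives no antibody incidence. If only subjects with an assigned titre are correlated, which 12.1 permits, the pooled false-positive rate falls to about 6–8% (log-titre SD of 1.5 doublings assumed), though power is then low. The ratio is no cure for noise: for a 39% loss its power is about 33–38% at a within-subject SD of 0.40 and 25–26% at 0.50. These points limit the severity. They do not make the unstratified correlation a good choice.

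**Stronger readings a reader might infer, which the documents do not support:**

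- *Mann-Whitney cannot serve because there are three arms.* Section 5.1 speaks of two dose levels, and 30 against 60 µg is a natural and valid comparison. The gap is only that the groups are not named.
- *It should become an ordered three-arm (Jonckheere-Terpstra) test.* That tests a different null hypothesis, which unexposed placebo subjects can drive. With no antibodies on placebo and identical rates of 40%, 60% or 80% at both doses, the ordered test rejects in 11%, 25% and 39% of trials at one-sided 2.5%. Mann-Whitney of 30 against 60 µg stays at 1–2%.
- *Placebo subjects inflate the correlation.* They would, as tied low pairs, but 12.2 concerns the drug's Cmax and placebo subjects have none.
- *The tests contradict a ban on inference.* Section 9.1 expressly exempts 12.2. What remains is loose wording in 9.2 and 11.2 and a synopsis without the exemption.
- *The correlation measures only dose.* It mixes dose with the within-dose association.

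**Conclusion.** The point holds for the titre–Cmax analysis, conditionally: if titre rises with dose, the unstratified correlation is confounded. The direction follows from the protocol's own exposure data; the rates in the working are illustrative. Antibody rates, titre shift and variance components are assumed, and the Cmax ratio is borrowed from total exposure. Both models agree on the mechanism, and both show nominal error once dose is removed.

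For dose against titre, the planned test is sound once its two groups are named. The statements on inference need only editorial alignment. Overall severity is low to moderate: the analyses are exploratory, but they serve a component of the primary objective and the better analysis needs no new data.

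**What to change.** 1. **Titre and exposure (12.2).** In ShK-186 subjects only, compute Spearman's correlation between the Day 29 pre-dose titre, with antibody-negative ranked lowest, and each subject's Day 29/Day 1 Cmax ratio. Show the plot by dose. Where Day 1 Cmax is missing, fall back on a dose-stratified Spearman correlation using Day 29 Cmax.
2. **Dose and titre (12.2).** Keep Mann-Whitney and state that it compares 30 with 60 µg.
3. **Editorial.** Carry the exemption for Section 12.2 in 9.1 into the synopsis, 9.2 and 11.2.

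The cost is wording in the protocol or SAP. The Cmax samples on Days 1 and 29 and the Day 29 pre-dose antibody sample are already scheduled (14.1.3, 14.1.7).
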